## Participants

### Inclusion criteria

Infants fulfilling all the following inclusion criteria will be enrolled in this trial: (1) infants born at study hospitals; (2) monozygotic twins (this will be confirmed by ultrasonographic diagnosis before birth and confirmed again with obstetricians during and after delivery, as monochorionic diamniotic twins and monochorionic monoamniotic twins are both monozygotic twins; therefore, both will be eligible) (24); (3) gestational age (GA) < 32 weeks (GA was calculated based on the date of the last menstrual period of the mother and an ultrasonographic screening performed during the first trimester of pregnancy); (4) those enrolled within the first 24 postnatal hours; (5) those free of severe perinatal asphyxia (defined as an Apgar score of 0–3 for more than 5 min, a cord blood gas pH < 7.00, or both); (6) those free of severe congenital anomalies or genetic syndromes; (7) those free of mother infections such as chorioamnionitis, TORCH syndrome (chorioamnionitis, TORCH syndrome, were diagnosed as previously described (24, 25); (8) written informed consent is obtained from the parents or guardians of the infants; (9) either of the twins has available UCB, and the cell number should be at least 5 × 10^7^ cells per kilogram.

### Exclusion criteria

Infants will be excluded from the study if (1) they exhibit severe congenital abnormalities (detected *via* prenatal ultrasound); (2) their condition is critical and are expected to die within the first 24 h; (3) they are diagnosed with twin-to-twin transfusion syndrome confirmed by prenatal ultrasonography (24).

### Ethical approval

This study is approved by the ethics committee of the Guangdong Women and Children Hospital. The ethics number is 202101265.

### Sample size

Our previous study showed that ACBMNC infusion was effective in reducing respiratory support duration in preterm infants (18). A randomized study in Korea by Won Soon Park showed that severe BPD incidence significantly reduced from 53% to 19% with mesenchymal stem cell intervention in the 23–24 GW group (*n* = 33) (20). The rate of BPD among very preterm infants at our NICU was 30% (pA), which is similar to the incidence rate reported previously (26). The sample size of this study was determined for assessing the efficacy of ACBMNCs compared with placebo with respect to the primary outcome in order to decrease the incidence of BPD or death with a two-sided α level of 0.05% and 80% power. We expect the intended (or at least acceptable) effect of ACBMNC infusion to be at a rate of 20% decrease in the frequency of BPD. To achieve this rate, at least 60 patients per group will be required based on the following formula:n=(pA(1−pA)/κ+pB(1−pB))((z1−α/2+z1−β)/(pA−pB))2)

κ = nA/nB is the matching ratio; α is type I error; β is type II error, meaning 1 − β is power.

Around 20 pairs of monozygotic twin births of less than 32 gestational weeks occur annually in Guangdong Women and Children Hospital and Dongguan Maternal and Child Health Hospital. Around 6 pairs of monozygotic twin births of less than 32 gestational weeks take place annually in Zhongshan Boai Hospital, Shunde Hospital, Southern Medical University, Dongguan Hospital, Southern Medical University, Nanfang Hospital, Southern Medical University, and Affiliated Maternal and Child Hospital of Foshan, Southern Medical University. Therefore, we assume that 60 pairs of monozygotic twins will be enrolled annually and the trial could be completed within 1 year.

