### Statistical analysis

Mean and standard deviation are reported for continuous variables, and the number and percentage are reported for categorical variables. Group comparisons of categorical variables for outcomes and co-interventions including death, BPD, and BPD severity are performed using nonparametric tests, the Fisher's exact test, or chi-square test, as appropriate. The relative risk (RR) is calculated as the ratio of the cumulative incidence rates of an event occurring in the intervention infusion group to the control group, and the number needed for treatment as the inverse of these two cumulative incidence rates. The results are shown as RR with 95% confidence interval (CI). For continuous variables, the mean values at each time point in each group of the variables are derived from a generalized linear model and the differences in the values over time are compared using an unpaired Student's t-test between the two groups. Kaplan–Meier cumulative incidence plots are generated to show time-to-event end points, namely, extubation and weaning to room air. All statistical tests are two-tailed, and *p*-values < 0.05 are deemed statistically significant. The Breslow–Day test and Cochran–Mantel–Haenszel (CMH) test will be used to adjust the data derived from different participating centers. The results will be reported as odds ratio (OR) with 95% CI. All statistical tests will be two-tailed and a *p*-value < 0.05 will be considered statistically significant. All statistical analysis will be performed using SPSS 21.0 (IBM).

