Our clinical studies and those of others have shown that cord blood-derived stem cell application is both safe and effective in the prevention of BPD in very preterm neonates (18–20, 27). Stem cells play a vital role in lung development, and their use for preventing or treating BPD has emerged as a promising therapy (15–21, 23, 27). However, the genetic heterogeneity between control and intervention groups may decrease the comparability between these groups, thereby reducing the statistical power of the therapeutic value of cord blood stem cells, especially in small sample trials (22). As various factors affect the complex molecular signals involved in the developing lung, the pathophysiological basis for BPD is manifold (6, 7). In this study, the intervention time point is the first 24 h after birth; our aim is to observe the preventive effect on BPD, and we will keep the postnatal medical treatment of twins to the maximum consistent according to the centers’ guideline. Furthermore, in the exclusion criteria, twins diagnosed with twin-to-twin transfusion syndrome confirmed by prenatal ultrasonography are also excluded. All these measures aim to minimize the environmental impact on the results. Genetic susceptibility to BPD is suggested by several studies on twins (22, 34), and there is an ongoing search for the role of genetic susceptibility to BPD (22, 35–37). Although in randomized control trials, baseline characteristics could be standardized or corrected for, it is difficult to evaluate or correct genetic predisposition. To treat very preterm monozygotic twins randomly could make the genetic predisposition distribution as similar as possible in two groups. As we know, monozygotic twins are regarded as the best research objects in clinical studies (38). Similar to a single-birth patient study, the different environment exposures or different growth rates will be balanced by the randomization and double-blinded characteristics between groups. As the genetic background in monozygotic twin premature infants is the same, the random enrollment of each of the twins in the placebo and MNC intervention groups will reduce the interference of genetic difference on assessing the protective effect of MNC on lung development and the outcome of BPD. This contributes to enhancing the statistical power of the therapeutic effect of cord blood stem cells and reducing the required sample size.

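### The sample-size paragraph misstates the inputs behind 60 per group: alpha is printed as 0.05%, the 20% decrease is not labelled absolute, and a BPD-only rate serves a death-or-BPD endpoint

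*Protocol article*

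**What the plan says.** In the protocol article, the Sample size section names the primary outcome as the target and sizes the trial to "decrease the incidence of BPD or death with a two-sided α level of 0.05% and 80% power". The control rate is local: "The rate of BPD among very preterm infants at our NICU was 30% (pA"). The effect is put "at a rate of 20% decrease in the frequency of BPD"; it is not called absolute or relative, and no value of pB is printed. The printed formula is for two independent proportions, and the stated result is at least 60 patients per group.

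Three other sections bear on this:
- Statistical analysis sets the test level: "All statistical tests will be two-tailed and a" p-value below "0.05 will be considered statistically significant".
- The abstract and Outcome measures make survival without BPD the primary outcome, so a death counts as a failure.
- The Discussion says that within-pair randomization contributes to "enhancing the statistical power of the therapeutic effect of cord blood stem cells and reducing the required sample size".

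**The concern.** The paragraph prints alpha, power, control rate, effect, endpoint and formula, so it can be checked as it stands. Three of these items conflict with each other or with the rest of the article. Alpha differs by a factor of 100 from the level used in the analysis. The effect has two readings that lead to very different sizes. The control rate and the effect describe BPD, while the endpoint is BPD or death.

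At stake is what the stated 80% power means. If the trial shows no significant difference, its reading depends on the effect it was built to detect. A reader who takes the 20% decrease as relative would believe that a modest effect had been looked for with good power. The calculation in fact rests on removing two-thirds of BPD cases.

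**Working it through.** **Inputs.** pA = 0.30, power 80% and alpha as printed (0.0005) come from Sample size; alpha = 0.05 comes from Statistical analysis; kappa = 1 follows from the 1:1 allocation. pB is not given: it is 0.30 − 0.20 = 0.10 if the decrease is absolute and 0.30 × 0.80 = 0.24 if relative.

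**Formulas.** Size per group, as printed, with kappa = 1:
n = [pA(1 − pA) + pB(1 − pB)] × [(z(1−α/2) + z(0.80)) / (pA − pB)]²
Power at 60 per group: Φ(|pA − pB| / SE − z(1−α/2)), where SE = √{[pA(1 − pA) + pB(1 − pB)] / 60}.
z(0.80) = 0.842; z(1−α/2) = 1.960 at 5% and 3.481 at 0.05%.

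**Step 1: reproduce the plan's figure.** Alpha 5%, 30% to 10%:
n = (0.21 + 0.09) × (2.802 / 0.20)² = 58.9, so 59, which agrees with 60.
SE = √(0.30 / 60) = 0.0707; power at 60 = Φ(2.828 − 1.960) = 80.7%.

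**Step 2: alpha as printed.** Alpha 0.05%, 30% to 10%:
n = 0.30 × (4.322 / 0.20)² = 140.1, so 141; power at 60 = Φ(2.828 − 3.481) = 25.7%.
The usual variants (one-sided, pooled variance, continuity correction) do not bring this near 60.

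**Step 3: the decrease read as relative.** Alpha 5%, 30% to 24%:
n = (0.21 + 0.1824) × (2.802 / 0.06)² = 855.5, so 856; power at 60 = Φ(0.742 − 1.960) = 11.2%.

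Of these readings, only alpha 5% with a 20-point absolute drop yields 60. That drop is 0.20 / 0.30 = 67% in relative terms, a relative risk of 0.33.

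**Step 4: the composite endpoint.** Any death without BPD raises the control rate of death or BPD above the BPD rate. The article gives no mortality or composite rate, so 35% and 40% are assumptions (5 or 10 points of death without BPD). Alpha is 5% throughout, and the printed formula is used.

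| Control rate (assumed) | Effect kept | Treated rate | n per group | Power at 60 |
|---|---|---|---|---|
| 35% | 20 points | 15% | 70 | 74% |
| 40% | 20 points | 20% | 79 | 69% |
| 35% | relative risk 0.33 | 11.7% | 48 | 88% |
| 40% | relative risk 0.33 | 13.3% | 40 | 93% |

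The direction of the change depends on which form of the effect carries over to the composite.

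**Step 5: pairing.** The formula treats the arms as independent, although each pair supplies one infant to each arm. For 60 pairs at 30% versus 10%, an exact mid-p McNemar calculation gives power of 79%, 88% and 96% at within-pair correlations of 0, 0.2 and 0.4 (assumed values; the article gives none). The independent-groups formula is therefore roughly neutral to conservative here. With a 20-point drop from the assumed composite rates, the same test gives 81% and 92% (35% versus 15%) and 75% and 88% (40% versus 20%) at correlations of 0.2 and 0.4.

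**The case against.** The strongest reply is that the first two items are wording slips and that 60 stands. The 5% level appears twice in Statistical analysis. With pA, n and the formula printed, a careful reader can recover pB = 0.10. The cited cell-therapy precedent, severe BPD falling from 53% to 19%, is also a large absolute effect (34 points, 64% relative). This is right as far as it goes. The sizes of 141 and 856 show what the printed words imply; they are not the trial's true requirement. A reader might infer from them that 60 was miscalculated, and Step 1 shows that it was not. Still, the reader should not have to work backwards to learn that alpha is wrong by a factor of 100 or that the target is a two-thirds reduction.

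A reader might also infer that the composite endpoint leaves the trial underpowered. The article does not support that: it gives no death rate, and Step 4 moves power down or up according to the effect assumed. What stands is that the 80% is not shown for the primary endpoint.

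Nor does the independent-groups formula show a shortage of patients, since pairing tends to help. The 73% power of Fisher's exact test at 30% versus 10% is no argument either: the chi-square test, which Statistical analysis also names, gives 80%, and about 12 expected events per arm make it suitable.

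**Conclusion.** The point holds as one about misstated inputs. Alpha contradicts the analysis section and is almost certainly a slip for 5%. The effect must be read as 20 absolute points, because the relative reading would leave 11% power at 60. With those two corrected, 60 per group follows, with 81% power for BPD alone falling from 30% to 10% in independent arms.

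The third item is the substantive one. The stated power rests on a BPD-only rate and effect, while the primary outcome also counts death. Its size cannot be fixed from the article. By the printed formula, with an assumed composite control rate of 35–40%, power at 60 ranges from 69–74% (20-point drop kept) to 88–93% (relative risk 0.33 kept), before any gain from pairing. Neither a wrong sample size nor a loss of power is established.

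**What to change.** Keep 60 pairs and rewrite the Sample size paragraph:
- State alpha as 5%, two-sided.
- Print pA and pB for death or BPD, with pA taken from the same NICU data as the 30%. Do not carry over 30% to 10%, which belongs to BPD alone.
- Label the effect as absolute percentage points and give the matching relative risk.
- Restate the power at 60 pairs for that composite under both effect assumptions, a fixed absolute drop and a fixed relative risk.
- Say that the printed formula treats the arms as independent and so takes no credit for the within-pair correlation on which the Discussion relies.

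The cost is one rewritten paragraph and a look-up of the local composite rate. No patients are added. The stated power may become less favourable.

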### Randomization

The randomization sequence will be generated electronically using SPSS (version 21). Following enrollment, the subjects will be assigned to treatment levels or groups after the verification of their eligibility and consent status. A random number will be assigned by computer for each pair of enrolled twins. For each pair, one random number will be assigned to the first baby of the twins; if the last number of this random number is odd, the first baby will be assigned to the intervention group, and the second baby of the twins will be automatically assigned to the control group; in contrast, if the last number of this random number is even, the first baby of the twins will be assigned to the control group, and the second will be automatically assigned to the intervention group. Those enrolled in the ACBMNC group will receive an infusion of ACBMNC within 24 h after birth. Those in the placebo group will receive an infusion of a placebo solution consisting of normal saline with similar volume based on the cell number results in their cord blood after processing. The ell dose for all patients will be 5 × 10^7^ cells per kilogram (18, 27).

### Blinding

The study data will be reviewed by the hospital ethics committee during the trial. Nobody will be made aware of the treatment-group assignments of the infants. After the enrollment is confirmed, the research assistants of the respective project leaders will confirm the random number. There will be at least one research nurse and physician in each center. Research nurses and physicians who are aware of the allocation of treatment will not be included in the babies’ care team and they will not participate in making care decisions for the babies in the trial. They will be asked to prepare the processed cord blood MNC or normal saline. Infusion bags will be covered with shading bags and MNCs will be infused by using a light-blocking infusion tube after preparation, so that the nurses who carry out the infusion and all physicians who treat the baby are not aware of the treatment assignment (Figures 2B,C). The infusion is then done by the supervisor nurse of the patients. The staff who collect and analyze the patients’ data and who follow up the patients are also blinded with the assignment. What is more, the infants’ parents are also not aware of the assignment. Therefore, this study is a double-blinded one.

**Figure 2 F2:**
[figure not shown]
Cord blood processing flow diagram. (**A**) Cord clamping. (**B**) Cord blood collection. (**C**) Intrahospital transport. (**D**) MNC separation after centrifugation. (**E**) Parameter detection. (**F**) MNCs are infused by using a light-blocking infusion tube and placing an IV line vertically.

## Intervention

### Enrollment and umbilical cord blood collection and transportation

Written informed consent is obtained from the parents or guardians of all infants before delivery. For each monozygotic twin, neonatologists will be summoned at least 1 h before delivery, and their brief is to study patient data and confer with the obstetrician to verify whether the patients fulfill the enrollment criteria. An intrahospital transport team will be organized, which includes three neonatologists (one of them will be a senior physician). A transport incubator and ventilator with an air oxygen mixer and heater humidifier that can provide intermittent positive-pressure ventilation will be equipped for intrahospital transport from the delivery suite to the NICU in the same hospital (Figure 2C). Two blood-collection bags (WEGO, China) containing 28 ml of citrate-phosphate-dextrose anticoagulant and several blood-collection tubes are prepared.

After the neonates are delivered, delayed cord clamping is done for 30–60 s if the babies do not show severe asphyxia and do not need immediate resuscitation. After the twins are born and before the placenta is delivered, both umbilical veins are sterilized and then punctured with a 17-gauge needle. A part of the cord blood will be collected to the blood-collection tubes for clinical blood tests and single-cell RNA sequencing within 24 h after collection, and then cord blood is collected using a blood-collection bag (WEGO, China) by trained medical staff (Figures 2A,B).

Enrollment will be evaluated again by the neonatologists according to the inclusion and exclusion criteria. The blood-collection bag is closed and sealed after the collection is completed. The cord blood bag is labeled with the full name of the neonate, the hospital name, and the birth time and then placed in a cord blood storage container at 4°C storage and sent to the GDCBB within 2 hours. The GDCBB is a provincial, public cord blood bank with the clinical certification of the American Association of Blood Bank (AABB) and authentication of the Chinese Ministry of Health. The GDCBB has been equipped with a thermostat that is specifically used for cord blood transportation; it is able to maintain a temperature of 4°C during transportation. The transportation time duration (both from and back to the hospital) is within 2 hours depending on the traffic condition.

### Cord blood processing

Procedures for cord blood processing will be performed in accordance with cord blood bank guidelines as described previously (28).

Briefly, after arriving at the GDCBB, the blood bags are transported to a 10000-grade aseptic operational workshop *via* a transmission window. Two milliliter of cord blood is taken to detect viruses [human immunodeficiency virus, hepatitis B virus, hepatitis C virus, cytomegalovirus by polymerase chain reaction (PCR)] and bacterial infections (including *Treponema pallidum-*antibody detection or blood smear). The results are obtained shortly before the transfusion is started. The blood bags are then centrifuged at 4°C with a gravity of 50 g for 8 min in a low-temperature centrifuge (RT, Beckman, United States). Then, red blood cells are removed. After that, the blood bags are turned straight and centrifuged for 10 min in the same condition as before. Then, MNCs are obtained after the plasma is separated by using the plasma separation clip (Figure 2D). Finally, a 1 ml MNC sample is taken to determine the following parameters: MNC count (Sysmex XE-5000 automated flow cytometer, Japan), CD34 count (BD calibur flow cytometry, BD Bioscience, United States), colony-forming unit-granulocyte and macrophage (CFU-GM) count under an inverted microscope after being cultured in methyl cellulose medium (SIGMA-ALDRICH, United States), sterility detection by an automatic bacteria detector (Thermo Fisher 6240, MA, United States), and cell viability by using the 7-aminoactinomycin D detection kit *via* flow cytometry analysis (Figure 2E). After processing, if the cell number reaches at least 5 × 10^7^ cells per kilogram, the cells will be titrated according to the cell concentration in 5% albumin to ensure that the final infusion volume ranges from 5 to 20 ml/kg and stored in the transparent separation bag in a 4°C refrigerator and then transported in the thermostat used for cord blood transportation. The cord blood cells will be sent back to the hospitals where they are collected. The patients are finally enrolled in the allocation. Even if only one of the twins has enough cord blood for the purposes of study participation, both will be enrolled as part of the randomization process.

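### Pairs with only one adequate cord blood unit are randomised without regard to which twin has it, so in half of them, on expectation, the active twin has no qualifying autologous product, and neither the treatment rules nor the sample size allow for this

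*Protocol article*

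**What the plan says.** Four rules in the Protocol article bear on this.

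- **Eligibility.** Item 9 of Inclusion criteria is met when "either of the twins has available UCB, and the cell number should be at least 5 × 10^7^ cells per kilogram". Cord blood processing confirms that this is deliberate: "Even if only one of the twins has enough cord blood for the purposes of study participation, both will be enrolled", and they go into the randomisation together.
- **Allocation.** Under Randomization (and likewise Study design and settings), "if the last number of this random number is odd, the first baby will be assigned to the intervention group". The co-twin takes the opposite arm without a draw of its own, and an even digit reverses the two. Nothing in the rule refers to which twin has cells.
- **Active treatment.** Randomization states: "Those enrolled in the ACBMNC group will receive an infusion of ACBMNC within 24 h after birth". It gives a single cell dose for all patients, 5 × 10^7 per kilogram. Cord blood processing describes titration into an infusion product only for a unit that reaches this count.
- **Placebo.** Randomization gives the placebo infant "normal saline with similar volume based on the cell number results in their cord blood after processing".

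The Sample size section asks for at least 60 per group and makes no allowance for active infants who do not get the cells.

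**The concern.** The rules cannot all be followed in a pair where only one twin has enough cells. If the digit makes the other twin the active one, that infant is due an autologous infusion at a count its own unit did not reach, and the processing section describes no product for such a unit. The article does not say what happens next.

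The placebo rule has a smaller gap of the same kind. A below-threshold unit has a count, but conversion of cells into an infusion volume is described only above the threshold. How the matching saline volume is set for a placebo twin with a short unit is therefore unclear.

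Two things are at stake. If the allocation stands and the infant goes without cells, the comparison is diluted and the planned power is not met. If a site instead lets cell availability decide which twin gets the cells, the arm is no longer set by the random number, and the within-pair contrast on which the Introduction and Discussion base the design is lost. With no stated rule, different centres could act differently.

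**Working it through.** **Inputs.** From Sample size: pA = 0.30, ratio 1:1, power 80%, 60 per group. The effect is read as 20 percentage points (pB = 0.10) and α as two-sided 5%. These are the readings that return the stated size. The α as printed (0.05%) would give 141 per group, and a relative 20% decrease (pB = 0.24) would give 856. The share f of pairs with one adequate unit is not in the document; 10%, 20% and 40% are assumptions.

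**Step 1: the plan's own figure.** With the protocol's formula:

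n = (0.30×0.70 + 0.10×0.90) × ((1.960 + 0.842)/0.20)² = 0.30 × 196.2 = 58.9, so 59.

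The stated 60 is reproduced, with almost no slack. Power at 60 is Φ(0.20/√(0.30/60) − 1.96) = Φ(0.868) = 80.7%.

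**Step 2: chance that the active twin is the short one.** The digit is independent of which twin has cells, so in a one-unit pair the probability is 0.50. Simulation gave 0.501 when the first-born had the adequate unit in 50% of pairs and 0.499 when in 80%, so birth-order differences in yield do not matter.

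**Step 3: dilution.** Each pair supplies exactly one active infant, so the expected share of the active arm without a qualifying product is f/2. If those infants have the control rate and are analysed as randomised:

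pB(f) = 0.10 + 0.20 × f/2

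power(f) = Φ((0.30 − pB)/√((0.21 + pB(1 − pB))/60) − 1.96)

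| f (assumed) | Affected, of 60 | pB | Difference (points) | Power at 60 per group | n per group for 80% |
|---|---|---|---|---|---|
| 0 | 0 | 0.10 | 20 | 80.7% | 59 |
| 10% | 3 | 0.11 | 19 | 75.6% | 67 |
| 20% | 6 | 0.12 | 18 | 69.9% | 77 |
| 40% | 12 | 0.14 | 16 | 57.8% | 102 |

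**Step 4: pairs needed if both units must qualify.** Obtaining 60 two-unit pairs takes 60/(1 − f) currently eligible pairs: 67 at f = 10%, 75 at 20%, 100 at 40%. On its most generous reading, Sample size gives 2×20 + 5×6 = 70 monozygotic twin births a year below 32 weeks, before other exclusions and refusals. Read as group totals, it gives 20 + 6 = 26.

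**The case against.** The strongest reply is that random allocation survives. If every pair is analysed in its assigned arms, non-receipt leaves a valid comparison of assignment. That stands. A reader might infer that the trial no longer compares autologous infusion with placebo, or that its randomisation is already broken. The document does not support this: no section lets the twin with cells be given them out of turn. That route is a risk created by silence, not a stated rule.

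Other stronger readings also go too far.

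- Half of the whole active arm is not affected. The one half is an expectation within one-unit pairs only.
- A short placebo twin does not necessarily lack a cell count. Both cords are punctured and the count is taken after processing, which is how a unit is found to be short. Only the step from count to volume is unclear.
- A reader might suppose that yield follows infant size or placental share, so that availability would confound. The document says nothing on this, and the point does not need it.

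It can also be said that a below-threshold product, or the genetically identical co-twin's unit, might be used. The abstract calls the dose a target, and the Introduction stresses shared genetic material. But no section provides for either, and the co-twin's cells would not be autologous.

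Finally, the flow diagram is not shown and an article condenses a fuller protocol, so handling may be described elsewhere. The conflict is nevertheless between rules that the article prints, and another text could resolve it only by qualifying one of them.

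**Conclusion.** The concern holds as a conflict between stated rules. In a one-unit pair the active twin has no qualifying autologous product with probability 0.50, and the article neither says what that infant receives nor allows for it in the sample size. This part depends on no assumed figure.

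The size of the effect is conditional. With f between 10% and 40%, the expected number of affected active infants is 3 to 12 of 60, and power falls from 81% to between 76% and 58%, against the stated 80%. This assumes that affected infants get no benefit, that allocation stands, and that analysis is as randomised. It uses the protocol's formula, which treats the arms as independent; within-pair correlation would move the power levels but not the 0.50. On those terms the consequence is dilution and lost power, not an invalid comparison. Because the design needs 59 of its 60 per group, even a small share of one-unit pairs takes it below target.

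**What to change.** Before enrolment, reconcile item 9 of Inclusion criteria, Randomization and Cord blood processing. Two statistical routes are open.

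**(a) Keep one-unit pairs.** State that cell availability never changes the allocation, analyse all pairs as randomised, and restate power with the expected share of one-unit pairs. This costs a few sentences and an estimate of f. Restoring 80% would take 67, 77 or 102 pairs at f = 10%, 20% or 40%; staying at 60 means declaring the lower power.

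**(b) Randomise a pair only after both processed units meet the protocol's existing cell-number criterion.** Cord blood processing places final allocation after the counts are known, so no new procedure is needed. The cost is recruitment and a narrower population: about 75 currently eligible pairs at f = 20% and 100 at f = 40% to obtain 60. Both exceed the 70 births a year of the most generous reading, so the one-year estimate in Sample size would need revising.

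The two routes need similar numbers of pairs if 80% power is to be kept, so the choice turns on which population and comparison the sponsor wants. Under (a), the protocol must also say what a short-unit active infant receives and how the saline volume is set for a short-unit placebo infant. Those are clinical decisions for the sponsor.
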